# Objectives and rationale of the noninterventional study

## Background

### Introduction

The legislator rules that experience about the use of a medicinal product is to be systematically recorded and analyzed after the product has been approved (AMG Section 4 (23)). The resulting information about the occurrence of rare adverse drug reactions contribute greatly to drug safety. The data obtained can also provide valuable information about the actual, non-study-related use of the medication in the indication concerned as a form of quality assurance. The NIS data are therefore published in a recognized scientific journal after their scientific evaluation.

### Quality assurance in medicine

Quality assurance has at all times been a shared task of the medical community inherent in the practice of medicine. This was emphasized and reaffirmed at the 101st German Medical Assembly in 1998 in relation to the principles of quality of assurance in the exercise of the medical profession already adopted in 1993.

The joint comments of the German Medical Association and the National Association of Statutory Health Insurance Physicians in response to the inquiry of the Conference of Ministers of Health of July 1998 also refer, among other things, to the following principles of quality assurance:

(Point 3) The sole purpose of quality assurance is to secure and improve patient
care and is therefore not an end in itself.
(Point 6) Quality assurance presupposes valid data and close cooperation between all concerned.
(Point 7) Quality assurance is not primarily research, but a target oriented, innovative ongoing and interdisciplinary process in all areas of medical care. It utilizes scientific methods to develop and evaluate suitable measures for use in hospitals and medical practices.
(Point 8) Quality assurance must not be confused with measures to improve economy in the health system, even though an improvement in cost effectiveness can be achieved with quality assurance methods.

Endeavours to improve quality management in the health service should therefore be directed primarily towards supporting the activities of the service providers. To systematically achieve a high quality of results, in view of the increasing abundance of information in medicine and medical care, the physician requires – in addition to his/her own observations – support in order to "do the right thing at the right time at the right place" when addressing a specific situation.

The main components of a quality management system of this type which aims to continuously improve the care process are described in the "Quality Management Guideline for Contractual Medical Care" of the JFC (Joint Federal Committee) which came into force on January 1, 2006. In Section 2 it provides, among other things – as the objective of an internal institutional quality management system – the objective demonstration and measurement of the results of care. In Section 4 relating to the instruments of an internal institutional QMS, reference is made, among other things, specifically to the documentation of courses of treatment and advisory activities.

It is therefore logical that partners in the health service – physicians on the one side, medicinal product manufacturers on the other side – should jointly develop a documentation system in the form of an online noninterventional study with the aim of realistically representing the care of chronically ill patients with simultaneous controlling of technical drug safety aspects of the medications used.

### Hepatitis C

Chronic virus hepatitis C is a disease which often takes a clinically insidious course and threatens the affected patients mainly because of its late complications (liver cirrhosis, hepatocellular cancer). In June 2002, peg­interferon alfa-2a (Pegasys®) was approved for the treatment of chronic virus hepatitis C by the European Agency for the Evaluation of Medicinal Products (EMEA) on the basis of two international marketing authorization studies (Zeuzem et al. 2000, Heathcote et al. 2000).

In patients with chronic hepatitis C, Pegasys® is best used in combination with ribavirin.

Since January 2003, ribavirin Copegus® has been approved by the Federal Institute for Drugs and Medical Devices (BfArM) in Germany for combination with peg­interferon alfa-2a (Pegasys®) in the treatment of chronic hepatitis C.

The combination of Pegasys® and ribavirin is indicated in non-pretreated patients and in patients who have failed to respond to previous treatment with interferon alfa (pegylated or non-pegylated) alone or in combination therapy with ribavirin.

Monotherapy with peg­interferon alfa-2a is indicated mainly when there is intolerance or contraindications to ribavirin.

Pegylated interferon alfa-2a (Pegasys®) is administered to patients with genotype 1 and the more rarely occurring genotypes 4, 5 and 6 in the combination with ribavirin initially for 12 weeks. The decision whether to prolong the therapy by 36 weeks to altogether 48 weeks or to discontinue the treatment is based on an HCV-RNA assay: either the virus assay in week 12 is negative (equivalent to a reduction in the viral load below the limit of detection) or a reduction was achieved in the original serum HCV-RNA by 2 log steps (equivalent to 99 % of the baseline value before start of treatment).

Patients who did not show this defined "early virological response" (EVR) after 12 weeks will with very high probability (97 %) also not have any lasting therapeutic success after further treatment (Ferenci P et al. 2001, Fried MW et al. 2001). This procedure saves the patient unnecessary stress from treatment side effects and saves costs.

In patients with genotypes 2 or 3, on the other hand, such a high EVR of 97 % is achieved that no monitoring of the viral load after 12 weeks is recommended.

As regards the duration of treatment, a further multicentre international study for patients with genotypes 1 and 4 also confirmed a treatment duration of 48 weeks (Hadziyannis SJ et al. 2004).

Treatment over 24 weeks may be considered for patients showing an infection with genotype 1 and a low initial viral load (LVL) ( 800,000 IU/ml) or with genotype 4 or who become HCV-RNA negative ( 50 IU/ml) by week 4 and remain HCV-RNA negative up to week 24 (Jensen D et al. 2006, Ferenci et al. 2006).

A total treatment period of 24 weeks, however, may be associated with a higher risk of relapse than treatment over 48 weeks. In these patients, the tolerability of the combination therapy as well as prognostic factors such as the degree of fibrosis should be taken into account when deciding the duration of treatment. In patients with a genotype 1 infection and a high initial viral load (HVL) (>800,000 IU/ml), and who become HCV-RNA negative by week 4 and remain HCV-RNA negative up to week 24, a shortening of the treatment duration should nevertheless be considered with caution because the limited data available suggest that shortening the treatment in this patient population may have a significantly negative impact on the persistent virological response.

Patients with genotypes 2 and 3 are normally treated with a duration of 24 weeks. No difference in efficacy was observed compared to a 48-week treatment.

A shortened treatment for 16 weeks may be considered for such genotype 2/3 patients who show a low initial viral load (LVL) ( 800,000 IU/ml) and who are already HCV-RNA negative in week 4 ( 50IU/ml) and remain HCV-RNA negative up to week 16.

As with the possibility of shortening the treatment period for genotype 1, the tolerability and prognostic factors should also be taken into account with genotype 2/3 when deciding on a reduction of the treatment period.

For patients with genotypes 5 and 6 less well substantiated by studies, the same recommendations are given as for the genotype 1 with HVL.

Patients with HIV-HCV coinfection should be treated over 48 weeks regardless of the genotype. A treatment period of less than 48 weeks has not been adequately researched.

The recommended total duration for retreatment of previously treated patients is 48 weeks. Patients with a detectable viral load in week 12 of the retreatment should discontinue this retreatment.

If retreatment is considered for patients who are infected with virus genotype 1 and who fail to respond to previous treatment with pegylated interferon plus ribavirin, the recommended total duration of treatment is 72 weeks.

The following information on the dosage of ribavirin (Copegus®) in combination with peg­interferon alfa-2a (Pegasys®) can also be derived from the study of Hadziyannis et al.:

Patients with genotype 1 with a body weight of less than 75 kg should receive 1000 mg ribavirin (Copegus®) orally per day, and with a body weight above 75 kg should receive 1200 mg. This recommendation has so far also applied to the interferon-ribavirin combination treatment of patients with genotype 2 or 3. The current data now show that patients with genotype 2 or 3 require only 800 mg ribavirin (Copegus®) orally per day regardless of body weight if administered in combination with peg­interferon alfa-2a (Pegasys®). This change in the recommendation for the ribavirin dosage on combination with peg­interferon alfa-2a (Pegasys®) can reduce unnecessary stress from treatment side effects and can also lower costs.

Further international studies have demonstrated the high efficacy and good safety profile of peg­interferon alfa-2a (Pegasys®) in combination with ribavirin (Copegus®) in patients with normal GPT (Zeuzem et al. 2004) and in HIV/HCV coinfected patients (Torriani et al. 2004).

These findings have meanwhile been incorporated in numerous national guidelines, including the German guidelines, as well as recommendations of international associations for liver research (EASL, AASLD).

## Formulation of the research question

In part I and II of the observational study (ML17071 and ML19464) the actual condition of patient care was documented and evaluated. The large number of documented patients also made it possible to describe and analyze patient populations which previously had been represented only inadequately in studies and for whom only data from very small cohorts are available. (Hüppe et al. 2004, Hüppe et al. 2005, Hüppe et al. 2006 Hüppe et al. 2007, Meyer et al. 2007, Zehnter et al. 2004, Zehnter et al. 2005, Zehnter et al. 2006, Zehnter et al. 2007). However, it is found to be more favourable to modify the recording of certain data in such a way that statements of future analyses can provide more precise presentations than today.

The basic objectives of this noninterventional study have not changed in relation to ML17071 and ML19464.

Specifically, these are:

- As the main objective, the efficacy and tolerability of the treatment of chronic hepatitis C with peg­interferon alfa-2a (Pegasys®), usually in the combination with ribavirin (Copegus®), are studied in patients being treated by gastroenterologists and other physicians familiar with interferon therapy in specialized practices and hospital outpatient departments in the real-life setting.
  The everyday applicability of the study results can be verified by a descriptive comparison of the recorded data with the efficacy and tolerability data from clinical studies on peg­interferon alfa-2a (Pegasys®) alone or in combination with ribavirin (Copegus®).
- Knowledge is to be generated about the therapeutic habits in hepatitis C and about patient compliance. This is to allow a statement to be made regarding the quality of treatment of patients with hepatitis C in Germany. Conclusions are also to be reached regarding the quality of treatment in residential practice, expressed in relation to the data from hospital outpatient departments.
- Based on the treatment quality data, measures which lead to an improvement in the quality of care of patients with hepatitis C are to be developed in accordance with the existing therapy recommendations (Summary of Product Characteristics, consensus recommendations of the medical societies, recommendations based on recent study findings). These measures consist of further training events, provision of direct information about guideline compliant treatment of the patient during the internet assisted data documentation, regular analyses of the data to determine the current status and, if there are considerable deviations from the recommendations, treatment by supervising the project participants.
- In addition, root cause and error analyses are to be performed for individual participating medical practices or hospital outpatient departments to selectively optimize the quality of care in the treatment of hepatitis C with peg­interferon alfa-2a (Pegasys®) and ribavirin (Copegus®).
- Safety data on peg­interferon alfa-2a (Pegasys®) and ribavirin (Copegus®) are recorded systematically and matched against the known safety profile.

Medicinal product used in standard treatment of hepatitis C:

Pegylated (40 kDa) Interferon alfa-2a (Pegasys®)

Marketing Authorization Holder: Roche Pharma AG, Grenzach-Wyhlen (Germany)

Marketing authorization number:

EU/1/02/221/005 PEGASYS 135 microgram injection solution in a prefilled syringe in 0.5 ml solution – 1 prefilled syringe + 1 injection needle

EU/1/02/221/006 PEGASYS 135 microgram injection solution in a prefilled syringe in 0.5 ml solution – 4 prefilled syringes + 4 injection needles

EU/1/02/221/009 PEGASYS 135 microgram injection solution in a prefilled syringe in 0.5 ml solution – 12 prefilled syringes + 12 injection needles

EU/1/02/221/007 PEGASYS 180 microgram injection solution in a prefilled syringe in 0.5 ml solution – 1 prefilled syringe + 1 injection needle

EU/1/02/221/008 PEGASYS 180 microgram injection solution in a prefilled syringe in 0.5 ml solution – 4 prefilled syringes + 4 injection needles

EU/1/02/221/010 PEGASYS 180 microgram injection solution in a prefilled syringe in 0.5 ml solution – 12 prefilled syringes + 12 injection needles

54828.00.00 Copegus 200 mg film-coated tablets, HDPE bottles with 28, 42, 112 or 168 tablets

66105.00.00 Copegus 400 mg film-coated tablets, HDPE bottles with 14 or 56 tablets

The current Summary of Product Characteristics is enclosed with the documentation.

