# Synopsis

| AIMS/CTMS No.: | ML21645 – Amendment 2 |
| --- | --- |
| Title: | Noninterventional study for quality assurance in therapy of chronic hepatitis C with Peg-(40kd)-Interferon alfa-2a (Pegasys) and ribavirin (i.e. Copegus) at hepatology centers – a project in cooperation with BNG (Association of German resident Gastroenterologists, part III) |
| Version and Date: | 4.3 of 28.02.2013 |
| Sponsor: | Roche Pharma AG, Grenzach-Wyhlen |
| Objectives: | Indication: chronic hepatitis C  Medication: peg­interferon alfa-2a (PEGASYS), Ribavirin (COPEGUS)   - The main objective is to determine efficacy and safety of chronic hepatitis C treatment with peg­interferon alfa-2a (Pe­ga­sys®) – usually in combination with ribavirin (Cope­gus®) – in patients treated by gastroenterology specialists in real-life setting. A descriptive comparison of the col­lected data with existing safety data and data from the approval of peg­interferon alfa-2a (Pegasys®) alone or in combination with ribavirin (Copegus®), will further establish the feasibility of the products in day-to-day practice. - In addition, information on hepatitis C therapeutic habits and patient compliance will be gained. Quality of treatment will be assessed by comparing data from clinical studies with data from physicians’ practice. Furthermore, the quality of treatment in physicians’ practices and hospital outpatient departments will be contrasted. - Direct measures will be developed –in accordance with existing treatment recommendations (SPC, consensus recommendations) – to improve the quality of care for patients with hepatitis C. These measures are training courses, direct notifications on guideline-conform treatment during the documentation of patient data, periodic analyses of data to determine the current status, and, if great deviations from the recommended therapy are observed, by project participant’s supervision. - Cause analyses and analyses of errors made by participating physicians in practices or outpatient departments will be performed to optimize the overall support quality for the therapy of hepatitis C with peg­interferon alfa-2a (Pegasys®) and ribavirin (Copegus®).   Data will be systematically collected to further refine the safety profile of peg­interferon alfa-2a (Pegasys®) and ribavirin (Copegus®). |

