## Rationale for choice of method

This trial is therapeutically and diagnostically noninterventional. The procedure followed by the involved physicians is not influenced by this trial. The physician is completely free in his/her decision regarding which patients he/she treats with the medication observed in this trial, which doses he/she chooses, which diagnostic measures he/she takes, how he/she monitors the course of treatment or which concomitant or additional medication he/she prescribes. The appointments for the physician-patient contacts are determined individually. The documentation time points are scheduled.

The choice of this methodological approach in the noninterventional study necessarily follows from the subject of investigation, which is to collect scientific data reflecting the clinical routine as far as possible.

Recording of data on the course and outcome of treatment in daily medical practice can only reflect reality in a noninterventional study. The decisive criterion for this is the inclusion of a large number of gastroenterology or other specialized practices and hospital outpatient departments experienced with interferon treatment, which are deliberately not chosen to comply with the strict requirements of a clinical study and which routinely treat hepatitis C patients. Moreover, access to patients is on an open basis; data are recorded for patient populations that reflect a majority of the hepatitis C patients in Germany, but who are normally not investigated in clinical studies because of strict inclusion and exclusion criteria (e.g. addiction patients or HIV-HCV coinfected patients).

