## Procedure

This trial does not influence the individual course of treatment. The noninterventional study has no influence on the medical decisions and procedures. The participating physician is requested, however, to document the decisions and measures taken in the case record form of this noninterventional study.

The documents attempt to reflect the usual course of treatment as closely as possible and thereby facilitate documentation. Under no circumstances are they to be misunderstood as instructions for the management of treatment.

The documentation procedure per patient is as follows:

1. the diagnosis is made and the treatment decision is taken outside the study
2. patient informed consent
3. patient status and statement regarding start of study
4. any interim findings
5. patient status and information on treatment at end of study. The final documentation should generally be performed 48 – 72 weeks after the start of the study or at the end of the treatment, if this is sooner.

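### The protocol says the study does not influence treatment but builds in guideline notices, training, feedback and supervision, so its habit and quality results may describe care under a quality-assurance programme

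*Protocol*

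**What the plan says.** Two parts of the protocol describe the study's relation to treatment differently.

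**No influence.** Section 4.3 states: "The procedure followed by the involved physicians is not influenced by this trial". Section 6.2 repeats it: "The noninterventional study has no influence on the medical decisions and procedures". Neither sentence is qualified. Both sections go on to stress the physician's freedom to decide and that the forms are not treatment instructions.

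**Measures meant to change care.** Section 4.2 lists, as an objective, measures to improve the care of hepatitis C patients. They comprise training events, "provision of direct information about guideline compliant treatment of the patient during the internet assisted data documentation", regular analyses of the data, and, "if there are considerable deviations from the recommendations, treatment by supervising the project participants". A further objective is that "root cause and error analyses are to be performed for individual participating medical practices or hospital outpatient departments", with the aim of improving care at those sites. The Synopsis confirms the in-system notices: "direct notifications on guideline-conform treatment during the documentation of patient data".

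**The objective that is affected.** Section 4.2 also says: "Knowledge is to be generated about the therapeutic habits in hepatitis C and about patient compliance". This is to support a statement on treatment quality in Germany and a comparison of resident practices with hospital outpatient departments. The main objective places efficacy and tolerability in the real-life setting.

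**The concern.** A study that shows a physician guideline information while recording how that physician treats may alter what it records. If so, a table of therapeutic habits or guideline conformity describes practice under the programme, and a reader who relies on 4.3 and 6.2 would take it as routine practice. The main risk is that treatment quality looks better than it would without the programme. The contrast between practices and hospital outpatient departments could also be affected if notices, feedback or supervision fall unevenly on the two.

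**Working it through.** The protocol states no figure on this point, so there is none to reproduce. The check compares sections and asks whether the measures could act before the decisions that are recorded.

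**1. Can both sets of statements be true?** Sections 4.3 and 6.2 deny influence on procedures and decisions. Section 4.2 and the Synopsis set up measures whose purpose is to bring treatment closer to recommendations. If the measures work as intended, the denial is wrong as worded.

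**2. Can a measure precede a recorded decision?**
- The Synopsis gives ten documentation points: baseline, weeks 2, 4, 8, 12, 24, 36 and 48, end of treatment, and end of follow-up.
- Section 7.1 requires prospective entry and has the software reject dates more than three months old.
- Section 6.2 places diagnosis and the treatment decision before documentation begins. A notice therefore cannot affect the initial choice in the patient being entered. It can affect later decisions in that patient, and any decision in the centre's later patients.

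**3. How often could a centre meet the measures?** Inputs: at least 9000 patients (8.1) and about 600 centres (5.1).
- Patients per centre: 9000 / 600 = 15 on average.
- Documentation sessions per centre: 15 × 10 = 150 at most. This is an upper bound, because many patients are treated for less than 48 weeks.

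Repeated exposure is therefore possible, within and between patients.

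**4. Is exposure recorded or named?** The practice characteristics (7.2.1) cover facility type, specialties, caseload and cooperation. The visit items (7.2.2) cover the patient. Section 7.3 names only patient factors as influencing variables. None of these lists a notice, or a date of training, feedback or supervision. Section 9 promises a presentation of interfering variables without naming these measures. The baseline form does record the consent date and the start of treatment (7.2.2), so calendar period and patient order within centre can be derived from data already held.

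**5. Can the size be derived?** No. The documents give no conformity rate and no effect of the measures. As illustration only, let p be the unprompted conformity and c the share of deviating decisions that are converted. The shift is (1 − p) × c. With an assumed p = 60%:

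| Assumed c | Shift in observed conformity |
| --- | --- |
| 2.5% | 40% × 2.5% = 1 point |
| 10% | 40% × 10% = 4 points |
| 30% | 40% × 30% = 12 points |

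The 95% sampling half-width at n = 9000 is 1.96 × √(0.6 × 0.4 / 9000) ≈ 1.0 point, before any allowance for clustering by centre. The shift may be negligible or large beside it, depending wholly on assumed inputs.

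**The case against.** The strongest defence is that the no-influence sentences mean only that the study prescribes nothing. Section 4.3 goes straight on to the physician's full freedom, 6.2 says the forms are not instructions, and 10.2 concerns legal status as noninterventional. The title and section 4.1.2 openly declare a quality-assurance purpose. This reading is fair as to intent. It does not remove the conflict, because freedom to decide is not absence of influence and the measures exist to influence.

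Other objections stand and limit the point:
- Section 4.2 describes the measures as still to be developed from the treatment data and gives no start date. A reader might infer that notices ran at every form from the first day; the text does not say so. Supervision is conditional on considerable deviations.
- Entry may lag by up to three months, and section 11 advises paper first and allows a study assistant to make the transfer. A notice may therefore arrive late or reach someone who makes no treatment decisions.
- A reader might infer that all cases will be pooled. Section 8.3 does not say this; it is a short descriptive outline, and stratification may be set in an analysis plan not shown here.
- A reader might fault the study for being unable to show whether the measures improved care. Evaluating them is not a stated objective.
- A reader might conclude that bias dominates sampling error. The illustration above shows that this rests on inputs the documents do not supply.

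**Conclusion.** The protocol contradicts itself on whether the study influences treatment, and the contradiction bears on the therapeutic-habits and treatment-quality objective. Those results may reflect care under a quality-assurance programme. The likely direction is towards guideline conformity, which follows from the purpose of the measures and not from data. The size, and the date from which any influence began, cannot be derived from the documents.

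The stronger claim, that the study cannot report real-life habits at all, is not supported. Early data may be unexposed, initial treatment decisions are partly protected, and a split by time uses data already held. The conclusion assumes only that the measures were put into effect for at least some centres while their patients were being documented.

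**What to change.** 1. **Wording.** In 4.3 and 6.2, state that the study prescribes no treatment but provides guideline information, training and feedback that may affect decisions. Describe the results in the report accordingly.
2. **Exposure dates.** From existing records, where available, compile the date the notices went live and the dates of each centre's training, feedback and supervision. Add these to the influencing variables in 7.3 and address them in the report. A new prospective log would come too late for most decisions: the protocol is version 4.3 of 28.02.2013, and the planned last patient in was 31/12/2011.
3. **Tables.** Show the therapeutic-habit and treatment-quality tables additionally by calendar period and by patient order within centre, and before versus after first exposure where dates exist. Note that centres continuing from parts I and II, whose basic objectives 4.2 describes as unchanged, may already have been exposed, so their first patients here are not necessarily unexposed.

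**Cost.** A text change, a compilation of dates, and additional tables from data largely in hand. The early or unexposed estimates will rest on fewer cases and will cover later decisions and outcomes (duration, stopping, SVR) less well. If no dates can be recovered, the wording change and the split by calendar period and patient order remain feasible.
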